#### Methods for Dealing with Adverse Events

During the informed consent process, at the end of each follow-up interview and in the beginning of each intervention session, study staff will remind participants to report any physical or social harm to the study staff immediately, so that participants may receive counseling and/or other assistance. A study psychiatrist and physician will both be available to study participants for the duration of the study; in cases where the psychiatrist or physician are not trained or equipped to treat the participant, referrals will be made. Participants also are asked whether they have suffered any social harm or adverse impact from the study as a routine part of follow-up interviews. Information on arrest, incarceration and drug overdose will be collected as part of the baseline and follow-up study questionnaires.

When an adverse event is reported to the study staff, the staff will investigate the details of the event and will reach a conclusion to whether the occurrence of the event was related to participation in the study. They will refer the participant to medical, psychological or social services as deemed appropriate, and if necessary, the investigators may take action to terminate the participant from the study. All adverse events and serious adverse events will be reported to the local Principal Investigator, [name] [name] within 24 hours orally or by email. A completed written report of the event will be sent to the Principal Investigator, [name] within 72 hours, and to the National Institute on Drug Abuse Project Officer, the Data Safety Monitoring Board and to the Institutional Review Boards within one week.

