**Figure 1. Study Design**

[figure not shown]

Among participants who are randomized to the intervention arm and who return for their follow-up assessments, we will conduct qualitative interviews among 10 participants at each follow-up visit. The purpose is to explore participants' experiences with injecting and sexual behavior changes and HIV-related stigma.

To assess operational outcomes across study arms, we will compare participants' perceived quality of sessions, proportion of IDUs attending all posttest counseling sessions and cost of service provision and opportunity cost incurred by participants. We will use ongoing in-depth interviews with a subset of our participants, analysis of project records, including participant evaluation forms, counseling and session log forms and financial records. Outcome evaluation will include pre-intervention assessment of participants with post-intervention follow-ups at 3, 6, 12, 18 and 24 months.

To assess HIV incidence among HIV-negative injecting network members of HIV-positive IDUs, injecting partners of HIV-positive IDUs enrolled in the intervention trial will be screened and tested for HIV status and a follow-up assessment will be conducted 24 months from the intervention start date of their respective index IDUs. Network members will be asked to provide a list of names of their injecting partners and their injecting practices with each partner over the past two years, enabling assessment of the possibility of network member's HIV exposure through injecting sources other than through the index participant.

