#### *Intervention Procedures:*

Individual level posttest counseling and support groups for HIV-positive IDUs: The individual level intervention consists of a sequence of posttest counseling and support group sessions that builds on an overall staged, sequential approach to behavioral change for HIV-positive IDUs. Posttest counseling will focus on coping and disclosure. Support groups sessions will focus on HIV knowledge and skill-building while simultaneously providing social support through shared experiences of being an HIV-positive IDU. Each participant in the intervention arm will participate in two 2-hour individual posttest counseling sessions and *three* 2-hour support group meetings consisting of 6-10 participants. Support group meetings will be conducted by a team of two facilitators; counseling sessions will be conducted by one of these same facilitators.

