### **Safety Monitoring:**

Safety monitoring will be performed by an independent Data Safety Monitoring Committee comprised of researchers from Hanoi and individuals in Thai Nguyen with expertise in issues relevant to this study.

The committee will meet initially to review the protocol prior to submission to the Thai Nguyen Centre for Preventive Medicine IRB and before data collection begins, after which it will convene to review the study within one year of commencing enrollment and at least annually thereafter. Emergency meetings of the committee will be convened as needed.

At each meeting review of interim reports, the DSM Committee will review the following in a report prepared by a statistician external to the study team:

- Expected versus actual accrual rates
- Study retention rates, total and by study arm (unblinded)
- Study outcomes, as available, total and by study arm (unblinded)
- Numbers of adverse events and serious adverse events, by type, total and by study arms (unblinded)
- Any quality assurance or regulatory issues that occurred since the previous review
- Any actions or changes with respect to the study protocol.

Blind interim analyses of the data will be conducted halfway through the follow-up period, where virtually all participants will have provided 6-month behavioral interim endpoints. Interim reports will be prepared for the DSM Committee by an external statistician and will be presented to the protocol team blinded as to study arm, labeled as "A", "B", "C" "D".

Consideration will be given to stopping the study under each of the following scenarios.

- Increases in the overall number of drug use and risk behaviors for all study participants, as compared to baseline levels, that are statistically significant at the  $p < 0.001$  level.
- Differences in study outcomes between the control arm (receiving neither intervention) and any of the three study arms that are statistically significant at the  $p < 0.001$  level.

- Differences in the number of serious adverse events (calculated by collapsing all SAEs) between the control arm (receiving neither intervention) and any of the three study arms that are statistically significant at the  $p < 0.001$  level. SAEs include mortality, suicide, accidents and violence.

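### The between-arm SAE comparison is exposed to differential ascertainment: harm reminders are tied to intervention sessions, and most serious events are not asked about alike in all arms

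*Protocol*

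**What the plan says.** All places are in the Protocol.

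- **Reminders.** Methods for Dealing with Adverse Events sets reminders during informed consent and then "at the end of each follow-up interview and in the beginning of each intervention session, study staff will remind participants to report" physical or social harm.
- **Visits.** The Phase II-IV design gives all index participants "post-intervention follow-ups at 3, 6, 12, 18 and 24 months".
- **Sessions.** Intervention Procedures gives the individual-level intervention "two 2-hour individual posttest counseling sessions and *three* 2-hour support group meetings". Description of Potential Benefits adds that men in both intervention arms may go back to counselors as often as they need. No session is described for men receiving neither intervention. Aims labels their arm attention-controlled, and Research Question describes the comparator as standard HIV counseling and testing.
- **Questions asked alike in all arms.** "Participants also are asked whether they have suffered any social harm or adverse impact from the study as a routine part of follow-up interviews". The next sentence adds: "Information on arrest, incarceration and drug overdose will be collected as part of the baseline and follow-up study questionnaires".
- **Use of the counts.** Among the scenarios for considering stopping, Safety Monitoring lists "Differences in the number of serious adverse events (calculated by collapsing all SAEs) between the control arm" and any of the other three arms, significant at p < 0.001. The DSM Committee also receives adverse event and SAE numbers by arm. Nothing limits these counts to events collected in the same way in every arm.

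**The concern.** A comparison of event counts is fair only if events have a similar chance of being recorded in each arm. Here one prompt to report is attached to the intervention itself, so arms with more sessions are reminded more often, by staff who know the assignment.

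The common interview does not fully even this out. Its general question is confined to harm attributed to the study, and the items free of attribution are arrest, incarceration and overdose. Safety Monitoring counts accidents and violence among SAEs, and the SAE definition includes hospitalization. For these, capture depends largely on a man volunteering a report, and extra reminders could increase that. A control man who had a traffic accident has no described program to attribute it to.

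Extra recording in an individual-level arm could look like harm from the intervention and could hide a true excess in the control arm. One of the affected arms is the combined arm, the subject of the primary hypothesis.

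**Working it through.** The protocol gives no SAE rate, no capture rate and no count of reporting occasions, so there is no stated figure to reproduce.

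**Step 1: reminders per man after consent, over 24 months**

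Inputs: 5 follow-up interviews (months 3, 6, 12, 18, 24); 2 + 3 = 5 individual-level sessions; 0 control sessions (assumption, since none is described).

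| Arm | Interviews | Sessions | Total | Ratio to control |
|---|---|---|---|---|
| Control | 5 | 0 | 5 | 1.0 |
| Structural only | 5 | 0 | 5 | 1.0 |
| Individual only | 5 | 5 | 10 | 2.0 |
| Combined | 5 | 5 | 10 | 2.0 |

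- Adding one consent contact: 11 / 6 = 1.83.
- By month 6, about where the interim analysis has behavioral data, and assuming all sessions fall before then (timing is not stated): (2 + 5) / 2 = 3.5.
- If control men had five sessions with the same reminder: 10 / 10 = 1.0.
- Open counselor access is not counted. It can only add contacts in the arms that have it.

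**Step 2: what each route covers**

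| Event | Asked at the common interview without attribution? |
|---|---|
| Arrest, incarceration, overdose | Yes |
| Hospitalization, accident, violence, suicide attempt | Not stated; only if the man attributes it to the study or volunteers it |
| Death | Not applicable; learned through tracing or contacts |

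**Step 3: how sensitive the p < 0.001 scenario would be (illustration only)**

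Assume no true difference in SAEs. Let λ be the expected number of SAEs recorded in control and r the capture ratio, individual-level arm to control. Counts are Poisson with means λ and rλ. Given a total N, the individual-level count is Binomial(N, r / (1 + r)), tested against 1/2 with a two-sided exact test. Chance of p < 0.001:

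| λ | r = 1.0 | 1.1 | 1.25 | 1.5 | 2.0 |
|---|---|---|---|---|---|
| 5 | 0.0002 | 0.0003 | 0.0006 | 0.002 | 0.011 |
| 10 | 0.0005 | 0.0006 | 0.0015 | 0.006 | 0.050 |
| 20 | 0.0006 | 0.0009 | 0.003 | 0.021 | 0.20 |
| 40 | 0.0007 | 0.0016 | 0.009 | 0.082 | 0.62 |

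A second version counts men with a reported SAE: 404 / 4 = 101 per arm, equal true risk, Fisher two-sided p < 0.001, both binomials enumerated exactly.

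| Capture, control v individual-level | True risk 40% | 20% | 10% |
|---|---|---|---|
| 50% v 50% | 0.05% | 0.04% | 0.02% |
| 80% v 90% | 0.23% | 0.10% | 0.06% |
| 50% v 75% | 3.5% | 0.7% | 0.2% |
| 40% v 80% | 22% | 3.7% | 0.6% |

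The 22% cell corresponds to 101 × 0.4 × 0.4 = 16 against 101 × 0.4 × 0.8 = 32 men. Every risk and capture rate is assumed. The tables show that the answer runs from negligible to large depending on figures the protocol does not give.

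**The case against.** A reader might infer that twice the reminders means about twice the recorded SAEs, so that the stopping comparison is biased as a matter of fact. The documents do not support that.

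- **A reminder is not a question.** It asks men to report harm at once. The systematic questioning sits in the follow-up interviews, on the same schedule in all arms, and an event first mentioned at a session might also surface at the next interview. This stands: 10 against 5 counts reminders, not events.
- **Control contact is unclear.** Besides the attention-controlled label, the design section compares session quality and attendance at posttest counseling across study arms, which hints at sessions outside the individual-level arms. This stands too. The 2.0 ratio is conditional; what is certain is only that no control sessions are described.
- **SAEs are mainly hard events.** Death depends little on prompting. Tracing contacts, follow-up visits in hospital or the rehabilitation center, and the study physician and psychiatrist are open to all arms. This stands for death, less so for accidents, violence and hospital stays: no record review is described, and the items free of attribution do not include them. Social harms are more sensitive to prompting. They fall outside the SAE scenario but inside the adverse event counts by arm.
- **Scope and consequence.** The structural-only arm has no individual sessions, so at most two of the three comparisons are affected. Crossing p < 0.001 leads only to consideration of stopping, with overall risks and benefits weighed. Both points stand.
- **Counting interview reports alone has its own risk.** It would set aside known SAEs, and with 20% drop-out planned for, it could become unequal if retention differs by arm. This stands and shapes the fix.

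**Conclusion.** The concern holds as a risk of differential ascertainment, not as a demonstrated bias. The text ties reminders to intervention sessions, asks about most serious events only through attribution to the study or spontaneous report, and then compares raw SAE counts with control. Equal collection cannot be inferred from what is written.

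If the control arm has no sessions, the imbalance is 10 against 5 reminders after consent in the individual-only and combined arms, and none in the structural-only arm. If the control arm has five matched sessions with the same reminder, it vanishes. The likely direction is more recorded SAEs in the individual-level arms. The size cannot be computed from the protocol. A false-crossing chance such as 22% should not be read as a property of this trial, since it needs both a 40% SAE risk and a 40% v 80% capture split, and the protocol supports neither. The change is worth making because it is cheap and protects a stated between-arm safety comparison.

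**What to change.** 1. At the scheduled follow-up interviews common to all arms, have the blinded assessment team ask every index man a fixed list of serious events (hospitalization, accident, violence, suicide attempt, overdose) without tying them to the study. Overdose is already in the questionnaires; the others would be added.
2. Trace deaths by the same procedure in all arms.
3. Add a field to the adverse event form recording where each report came from (interview, session, counselor visit, tracing, other).
4. In Safety Monitoring, base the primary between-arm SAE comparison on these commonly collected events. Show the DSM Committee the all-source counts by arm alongside, so that no known SAE is omitted, and read them together with retention by arm, which it already receives.
5. State what contact the control arm has, and whether it carries the same reminder.

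The session reminders stay, for participant care. The cost is a few questionnaire items, one form field, one extra table and a sentence on the control arm.

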#### Methods for Dealing with Illegal Reportable Activities

CPM has agreements with local law enforcement personnel to ensure that participants in HIV risk reduction programs are not arrested for participation in programs.

#### Samples Stored Beyond the End of the Study

A human biological materials repository for blood samples will be maintained at Johns Hopkins Bloomberg School of Public Health, under the direction of the PI, [name]. We would like to use these specimens to test for other health-related issues that may be related to HIV, hepatitis, or other sexually transmitted diseases using unspecified testing methods. A separate informed consent for specimen storage will be administered to the participant. Participants do not have to agree to sign the additional consent form for specimen storage to participate in this research study. Blood will be stored as coded for 5 years after the study is completed. Participants who agree will also be asked if they consent to be contacted for future studies. Consent forms will be used to assure that participants agree for their sample to be stored as well as to be re-contacted in the future. There are no plans to share the samples with other investigators.

#### **Risk/Benefits:**

##### **Phase I: Formative**

#### *Description of Risks and Measures to Minimize Risks*

During the interview, some participants may feel uncomfortable when asked personal questions about their sexual and injecting behavior histories. Participants may refuse to answer any question that they are uncomfortable answering, and may stop the interview at any time.

Potential exposure to police authorities during the study may place IDUs in a situation where they receive referral to a drug treatment program. However, commitment from both national and local officials on protecting confidentiality and careful measures to assure confidentiality, we anticipate few challenges and no problems with these issues. Furthermore, we have established ties to this community, and have a working relationship with the local People's Committees and police authorities.

We will also take steps to maintain strict confidentiality of information on participants' HIV status. These steps are outlined below under the Confidentiality Assurances heading.

#### *Description of Potential Benefits*

There are no direct benefits for participation in the formative phase of the study. However, the information will help to HIV prevention interventions that may improve the health of their community.

#### *Description of Level of Research Burden*

The burden of participation should be low, as the phase primarily consists of casual discussions among community members lasting one hour and hour-long interviews with men and women.

## **Phases II-IV: Baseline, Intervention and Evaluation**

### *Description of Risks and Measures to Minimize Risks*

As in qualitative interviews, participants completing the baseline and follow-up interviews may have a small risk of psychological distress posed by study questions concerning HIV risk, sexual and drug using behaviors. Participants may find answering questions about these issues upsetting; these questions will be asked in as sensitive a manner as possible. If a participant experiences emotional upset during the interview, the research staff will be trained on how to handle these situations and the local principal investigator, [name] [name] will be available to speak with participants if needed.

There are minimal physical risks to giving blood, such as a slight pain when the needle is inserted and possible bruising. To reduce the possibility of pain and bruising, blood draws will be taken by trained phlebotomists, and participants will be asked to rest and take water following the blood draw. Testing for HIV may cause anxiety and stress while waiting for test results, and participants who are told they are HIV-positive may experience emotional and social problems, such as depression and stigmatization. Pre and post-testing counseling by trained counselors will be provided to minimize these potential effects. In addition, a psychiatrist will be on call should a counselor feel that a subject is in danger of harming him- or herself or others during the course of a study visit.

Potential exposure to police authorities during the study may place IDUs in a situation where they receive referral to a drug treatment program. However, commitment from both national and local officials on protecting confidentiality and careful measures to assure confidentiality, we anticipate few challenges and no problems with these issues. Furthermore, we have established ties to this community, and have a working relationship with the local People's Committees and police authorities.

Because HIV-status is an inclusion criteria for participation in our study, we will take steps to maintain the strict confidentiality on all participants' HIV status. These steps are further outlined below under the Confidentiality Assurances heading.

### *Description of Potential Benefits*

IDUs participating in the survey and laboratory testing will receive free HIV testing and free treatment for opportunistic infections that may be related to HIV. The following treatments will be provided for opportunistic infections as appropriate: Co-trimomazol, Erythromycine, Ciprofloxacin, Flucanazole and Acyclovir. Participants may benefit from learning about HIV/STDs and ways to safely inject and have sex. IDUs in both intervention arms will also be invited to return to counselors as often as needed throughout the study period. At a community level, if the trial is successful there are potentially enormous social benefits that can be gained from the study. Specifically, at the end of our proposed study, we will have tested a multilevel intervention that is tailored to the social and risk-taking context of HIV-positive IDUs. MOH Life Gap, the primary agency for HIV programs in Vietnam, has indicated that our intervention is feasible and relevant in the Vietnamese context and could be sustained by the MOH. A demonstrated HIV risk reduction among HIV-positive IDUs may provide a model to stem the growth of the HIV-epidemic in Vietnam, which would benefit the community.

## **Compensation:**

Individuals participating in any phase of the intervention will be paid the equivalent Vietnamese Dong of \$6.50 US for each completed interview for the time they may have lost from work and the equivalent of \$1.25 US to cover transportation to the research facility.

## **Disclosure/Consent Process:**

### *Description of the Consent Process*

Our research staff has prior experience obtaining informed consent from IDUs for clinical trials within this cultural context. The informed consent procedures have been designed to maximize understanding of potential risks. All consent forms will be translated into Vietnamese and back-translated into English to ensure correct use of language.

Consent forms will be read aloud to participants by study interviewers. After reading the consent forms and prior to seeing a signature, interviewers will ask participants to summarize the study and explain the reasons why they want to participate. At this point, any misunderstandings regarding procedures, risk or benefits can be clarified. If there are cultural, literacy or political reasons why a signature is not appropriate, individuals will be allowed to mark the consent form with an "X." Informed consent will be obtained when data are collected including in-depth interviews, focus group discussion, the pre-screening assessment, and the baseline interview. At follow-up interviews participants will be reminded about the consent form that they signed initially and any misunderstandings will be clarified. Information sheets will be given to participants at each intervention session that include information about the research study.

